## 12.2 Populations for Analysis

### 12.2.1 Analysis Sets

The following populations for analysis are defined in [Table 13](#).

**Table 13 Populations for Analysis**

| Population                | Description                                                                                                                                                                                                                                                                                                   |
|---------------------------|---------------------------------------------------------------------------------------------------------------------------------------------------------------------------------------------------------------------------------------------------------------------------------------------------------------|
| Safety Analysis Set (SAF) | All randomized participants who received at least 1 dose of study treatment. Participants will be analyzed based on the treatment that they actually received.
The SAF will be used for all safety analyses.                                                                                               |
| Full Analysis Set (FAS)   | All randomized participants. Participants will be analyzed in accordance to the ITT principle, i.e., based on randomized treatment, irrespective of the treatment they actually received.
The FAS will be used for all efficacy analyses on efficacy endpoints and will serve as the primary analysis set. |

Abbreviations: FAS = full analysis set; ITT = intention-to-treat; SAF = safety analysis set

For the Part B exploratory analysis further analysis sets may be defined in the SAP.

### 12.2.2 Participant Disposition

The number of participants screened, randomized, randomized and treated, randomized and not treated, and the number of participants in the analysis sets will be summarized for all screened participants.

The number and percentage of participants will also be summarized for the following disposition categories:

1. Completed study treatment per-protocol;
2. Discontinued study treatment early and the reason for discontinuation;
3. Completed the study including post-treatment follow-up;
4. Discontinued from the study early and the reason for discontinuation.

The table will be presented by treatment arm using the FAS.

All participants' disposition data will be listed.

## 12.3 Statistical Analyses

The Statistical Analysis Plan (SAP) will be finalized prior to database lock for the primary analysis and will include a more technical and detailed description of the statistical analyses. This section

is a summary of the planned statistical analyses of the most important endpoints including primary and secondary endpoints.

### 12.3.1 General Considerations

For continuous variables, descriptive statistics (number of observations, mean, SD, minimum, first quartile, median, third quartile, maximum, and 95% CI, as appropriate) will be given. Categorical variables will be presented as counts and percentages with non-missing values in each category. The count of missing observations will be provided in all descriptive tables. For all statistical analyses, p-values and 95% CIs will be given.

For Part A, descriptive statistics will be presented by 5 treatment arms and by visits from Week 0 to Week 12:

- Arm 1: sonelokimab 120 mg Q2W;
- Arm 2: sonelokimab 60 mg Q2W;
- Arm 3: sonelokimab 60 mg Q4W;
- Arm 4: placebo;
- Arm 5: adalimumab 40 mg Q2W.

For Part B, descriptive statistics will be presented by 9 treatment arms and by visits from Week 0 to Week 24 and repeated by visits from Week 12 to Week 24:

- Sonelokimab 120 mg Q2W→sonelokimab 120 mg Q4W;
- Sonelokimab 120 mg Q2W→adalimumab 40 mg Q2W;
- Sonelokimab 60 mg Q2W→sonelokimab 60 mg Q4W;
- Sonelokimab 60 mg Q2W→sonelokimab 120 mg Q4W;
- Sonelokimab 60 mg Q4W→sonelokimab 60 mg Q4W;
- Sonelokimab 60 mg Q4W→sonelokimab 120 mg Q4W;
- Placebo→sonelokimab 120 mg Q4W;
- Adalimumab 40 mg Q2W→adalimumab 40 mg Q2W;
- Adalimumab 40 mg Q2W→sonelokimab 120 mg Q2W.

Baseline values will be defined as the last non-missing measurement prior to first dose of study treatment.

Change from baseline will be defined as the post-baseline visit value minus the baseline value.

All sensitivity analyses will be regarded as exploratory and no formal adjustment for multiplicity will be made. Details on sensitivity and planned subgroup analyses will be provided in the SAP.

All analyses will be performed using SAS® Software version 9.3 or later.

### **12.3.2 Primary Endpoints**

The primary efficacy endpoint is described in Section [7.2.1](#).

#### **12.3.2.1 Primary Analysis**

For the primary analysis, the hypotheses to be tested are that the proportion of participants who achieve ACR50 at Week 12 compared with baseline in the sonelokimab 120 mg Q2W, sonelokimab 60 mg Q2W, or sonelokimab 60 mg Q4W arms are different from that of the placebo arm.

Only the sonelokimab 120 mg Q2W, sonelokimab 60 mg Q2W, and sonelokimab 60 mg Q4W arms will be compared pairwise with placebo. A comparison among dose arms (sonelokimab 120 mg Q2W, sonelokimab 60 mg Q2W, and sonelokimab 60 mg Q4W) is not planned. [REDACTED]

A logistic regression model will be used to test the pairwise comparisons (placebo and either sonelokimab 120 mg Q2W, sonelokimab 60 mg Q2W, or sonelokimab 60 mg Q4W) including fixed effects for treatment and the stratification factors (sex and exposure to biologic agents prior to the Screening Visit). Results will be presented in terms of odds ratios, as well as risk difference, 95% CI, and estimated p-value.

For the primary analysis, a non-responder imputation method will be used. Participants will be considered non-responders to treatment if they discontinue the study prior to the Week 12 Visit due to any reason, have a missing ACR50 score at baseline or at the Week 12 Visit due to any reason, or take prohibited medication prior to the Week 12 Visit.

The sensitivity estimand for the primary endpoint will be analysis using a Generalized Linear Mixed Model (GLMM) to account for any missing data due to withdrawals for reasons other than lack of efficacy or taking prohibited medications. The model will include fixed effects for treatment, sex, prior biologic use, visit, treatment by visit interaction. The correlations between repeated measures will be modeled using an unstructured covariance matrix.

The primary analysis will be performed using the FAS.

#### **12.3.2.2 Type I Error Control for the Primary and Key Secondary Endpoints**

To adjust for multiple testing and to control the family-wise error rate, the Bonferroni-Holm method will be applied first to sonelokimab 120 mg Q2W (Arm 1) and sonelokimab 60 mg Q2W (Arm 2), followed by a step-down procedure to test for sonelokimab 60 mg Q4W (Arm 3). The

smaller of the p-values  $p_{\text{SLK120mgQ2W}}$  and  $p_{\text{SLK60mgQ2W}}$  will be compared to  $\alpha/2 = 0.025$ , and the greater p-value to  $\alpha = 0.05$ , where  $p_{\text{SLK120mgQ2W}}$  is the p-value resulting from the comparison between sonelokimab 120 mg Q2W (Arm 1) and placebo (Arm 4) and  $p_{\text{SLK60mgQ2W}}$  is the p-value resulting from the comparison between sonelokimab 60 mg Q2W (Arm 2) and placebo (Arm 4). If both  $p_{\text{SLK120mgQ2W}}$  and  $p_{\text{SLK60mgQ2W}}$  are significant then the testing procedure will continue with the key secondary endpoints. The Bonferroni-Holm procedure used for the primary endpoint will be applied to each key secondary endpoint sequentially. If the procedure passes all the key secondary endpoints for both doses then sonelokimab 60 mg Q4W (Arm 3) will be compared to  $\alpha = 0.05$  firstly for the primary endpoint and then sequentially through the key secondary endpoints.

### 12.3.3 Secondary Endpoints

#### 12.3.3.1 Key Secondary Endpoints

For the key secondary endpoints the hypotheses to be tested are that the proportion of participants who achieve the endpoints described in Section 7.2.2 at Week 12 in the sonelokimab 120 mg Q2W, sonelokimab 60 mg Q2W, or sonelokimab 60 mg Q4W arms are different from that of the placebo arm.

As per the primary analysis, only the sonelokimab 120 mg Q2W, sonelokimab 60 mg Q2W, and sonelokimab 60 mg Q4W arms will be compared pairwise with placebo. The adalimumab arm will serve as a reference arm only. A comparison among dose arms sonelokimab 120 mg Q2W, sonelokimab 60 mg Q2W, or sonelokimab 60 mg Q4W is not planned.

The statistical methods that will be used to test these hypotheses will be the same as described for the primary endpoint. The analysis of the key secondary endpoint PASI90 will only include the subgroup of participants with PsO involving at least 3% BSA at baseline. This is expected to be between 50% and 67% of the FAS.

A non-responder imputation method will be used as described for primary analysis of the primary endpoint.

The analysis will be performed using the FAS.

#### 12.3.3.2 Other Secondary Endpoints

For the other secondary endpoints, listed in Section 7.2.3, no confirmatory statistical testing will be performed, but statistical tests may be used for exploratory purposes only. All endpoints will be assessed at time points as outlined in the SOA in Section 3, Table 1, if not indicated otherwise.

All continuous endpoints will be summarized descriptively and analyzed using a mixed model for repeated measures (MMRM) including treatment arm, visit, sex, prior exposure to biologic agents and treatment by visit interaction as fixed effects. An unstructured covariance matrix will be used for the MMRM analysis, unless the model does not converge, in which case the covariance matrix will be decided upon model convergence status and the Akaike information criterion. The

least-squares means in each arm, the least-squares mean difference between arms, and its 95% CIs and p-values will be estimated by the model. Treatment effect estimates will be also extracted by visit.

All dichotomous endpoints will be summarized descriptively and analyzed using logistic regression with odds ratios, as well as risk difference and associated 95% CIs and p-values.

For dichotomous endpoints, a non-responder imputation method will be done and details will be defined in the SAP. For continuous endpoints, no imputation is planned.

FAS will be used for all other secondary endpoints analysis.

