## 8.6.1.2 Mixed Model Repeated Measures

Continuous efficacy endpoints assessed over time will be analyzed using an MMRM model including treatment arm, baseline, visit, sex, prior exposure to biologic agents and treatment by visit interaction as fixed effects and participant as random effect. An unstructured covariance matrix will be used for the MMRM analysis, unless the model does not converge, in which case the covariance matrix (e.g. variance components, autoregressive, compound symmetry, and Toeplitz) will be decided upon model convergence status and the Akaike information criterion.

The MMRM will be used to test for differences in the mean of the endpoint of interest (e.g. change from baseline in TJC68) between groups of interest (e.g. each active treatment group versus placebo).

From the model, the adjusted least squares (LS) means in each group and the difference in LS means for the group comparisons will be estimated together with 95% CIs for the differences and p-values for the pairwise comparisons. Treatment effect estimates will be also extracted by visit.

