#### **8.6.2.8 Hs-CRP**

Hs-CRP values are assessed at Baseline, Week 2, Week 4, Week 8, Week 12, Week 14, Week 16, Week 20 and Week 24.

Hs-CRP values which are recorded as <LLQ (i.e <0.10 mg/L) will be set to be half the value of the LLQ for these values (i.e 0.05 mg/L) for analysis purpose.

To test hs-CRP, the data will be log transformed prior to using a MMRM including as detailed in section 8.6.1.2. The results will be back-transformed to be presented in terms of adjusted least-squares (LS) geometric means, and ratios in LS geometric means together with 95% CIs and p-values.

If the data suggest that either endpoint is normally distribution rather than log-normally distributed then the analysis will be performed on the change from baseline without log-transformation.

The CRP assessments as well as the corresponding ratio to baseline will also be summarized descriptively by treatment group and visit for Part A and Part B.

The hs-CRP analysis will also be repeated, only including subjects with a baseline hs-CRP >ULN (5mg/L).

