#### **8.6.4.11 Modified Nail Psoriasis Severity Index**

The nNAPSI is a tool to assess nail involvement in participants with PsA with an index score ranging to 0 to 130 for all fingernails.

Three features or groups of features (pitting, onycholysis and oil-drop dyschromia and crumbling) or each fingernail will be graded on a score of 0 to 3.

The number of pits for each finger nail is scores as 0 = 0, 1-10 = 1, 11- 49 = 2 and >50 = 3.

The score percent of nail with crumbling present it scored as no crumbling = 0, 1-25% = 1, 26 – 50% = 2 and >50% = 3.

The score percent of nail with onycholysis and/or oil drop dyschromia is: none = 0, 10% = 1, 11-30% = 2, >30% = 3.

Four features (leukonychia, splinter hemorrhages, hyperkeratosis, and red spots in the lunula) will be graded as either present (1) or absent (0) in each fingernail.

The total score is calculated by summing the score for each feature and each fingernail.

The change from baseline in mNAPSI will be analyzed using the method described in 8.6.1.2 for subjects with nail psoriasis at baseline (mNAPSI > 0). Descriptive summaries by treatment group and visit will also be displayed for Part A and Part B. For Part A and B there will also be an LOCF summary of the mNAPSI to present the absolute, change from baseline and percent change from baseline by the randomized treatment arm.

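### The SAP's MMRM shares one baseline slope across all Part A visits; a baseline-by-visit term could sharpen Week 12 estimates for the multi-visit continuous endpoints at almost no cost

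*Combined protocol and SAP*

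**What the plan says.** Protocol 12.3.3.2 (Other Secondary Endpoints) describes the MMRM for continuous endpoints as "including treatment arm, visit, sex, prior exposure to biologic agents and treatment by visit interaction as fixed effects". Baseline is absent.

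SAP 8.6.1.2 specifies an "MMRM model including treatment arm, baseline, visit, sex, prior exposure to biologic agents and treatment by visit interaction as fixed effects". Baseline is now present as a main effect, with no baseline-by-visit term. The same section says: "An unstructured covariance matrix will be used for the MMRM analysis, unless the model does not converge". It also says: "Treatment effect estimates will be also extracted by visit". SAP Section 9, which lists departures from the protocol, does not mention the added baseline term.

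The status of these analyses is clear from protocol 12.3.3.2: "no confirmatory statistical testing will be performed, but statistical tests may be used for exploratory purposes only". SAP 8.1 plans no testing in Part B, so the tested contrasts are those of Part A.

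The number of Part A visits differs by endpoint (SAP 7.2):
- **ACR components:** Weeks 2, 4, 8 and 12. For hs-CRP, SAP 8.6.2.8 states: "Hs-CRP values are assessed at Baseline, Week 2, Week 4, Week 8, Week 12, Week 14, Week 16, Week 20 and Week 24".
- **PsAID-12, BASDAI, LEI and SPARCC:** Weeks 4, 8 and 12.
- **SF-36v2 and FACIT-Fatigue:** Weeks 4 and 12.
- **mNAPSI:** Week 12 only, although SAP 8.6.4.11 says: "The change from baseline in mNAPSI will be analyzed using the method described in 8.6.1.2".
- **LDI:** SAP 8.6.4.9 gives descriptive summaries and names no MMRM.

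**The concern.** The model lets the treatment effect differ by visit but not the effect of baseline. For change in a non-negative score, the slope on baseline usually steepens as patients improve, because change becomes more nearly proportional to the starting value and because later values are less correlated with baseline. A single slope is then a compromise across visits. If it is too shallow at Week 12, baseline variation stays in the Week 12 residual and the confidence interval is wider than the collected data require.

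At stake is the precision of the Week 12 estimates, mainly for the ACR components that help to explain the primary result, with about 40 participants per arm. The two documents also describe different models, and the difference is not declared.

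**Working it through.** **The plan's own figure.** The only stated precision figure is the ACR50 power: 40 per arm, 40% against 10%, two-sided alpha 0.025. Pooled SE = √(2 × 0.25 × 0.75 / 40) = 0.0968. Unpooled SE = √((0.24 + 0.09) / 40) = 0.0908. (0.30 − 2.241 × 0.0968) / 0.0908 = 0.91, so power is 82.0%, in line with the stated figure of more than 80%. It has no bearing on this point. The documents give no SD, correlation or precision for any continuous endpoint, so every input below is an assumption.

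**Formula (complete data).** Set the baseline SD to 1. Visit v has SD s_v and correlation r_v with baseline.
- Slope of change on baseline at visit v: b_v = r_v s_v − 1.
- R is the unstructured residual covariance given baseline. Its Week 12 variance is s₁₂²(1 − r₁₂²).
- Common slope fitted by the SAP model: b_c = (1′R⁻¹b) / (1′R⁻¹1).
- Week 12 variance, common slope over visit-specific slopes: 1 + (b₁₂ − b_c)² / [s₁₂²(1 − r₁₂²)].

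**Analytic cases, Weeks 2, 4, 8, 12.** Where SDs fall, they fall linearly from baseline to Week 12.

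| Assumption | b₁₂ | b_c | Ratio |
|---|---|---|---|
| All correlations 0.5, constant SD | −0.50 | −0.50 | 1.000 |
| All correlations 0.5, SD falling to 0.7 | −0.65 | −0.604 | 1 + 0.046²/0.3675 = 1.006 |
| Baseline correlation 0.70/0.65/0.60/0.55, visit correlation 0.6 | −0.45 | −0.355 | 1 + 0.095²/0.6975 = 1.013 |
| Same, visit correlation 0.7 | −0.45 | −0.348 | 1 + 0.102²/0.6975 = 1.015 |
| Baseline correlation 0.8/0.7/0.6/0.5, visit correlation 0.6 | −0.50 | −0.257 | 1 + 0.243²/0.75 = 1.079 |
| Same, visit correlation 0.7 | −0.50 | −0.220 | 1 + 0.280²/0.75 = 1.105 |
| Same fading, SD falling to 0.7, visit correlation 0.6 | −0.65 | −0.380 | 1 + 0.270²/0.3675 = 1.198 |

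With equal correlations of 0.5–0.8 and SDs falling to between 0.85 and 0.4 of baseline, the ratio is mostly below 1.02. The worst cell (correlation 0.8, SD falling to 0.62) is 1 + 0.061²/0.138 = 1.027.

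**Which visit sets the slope.** In the fading case with visit correlation 0.6, the weights on Weeks 2, 4, 8 and 12 are 0.53, 0.34, 0.16 and −0.03, so early visits dominate. With equal correlations and constant SD each visit has 25%. With equal correlations of 0.5 and SD falling to 0.7, Week 12 has the largest weight, 44%.

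**Simulation, 5 arms of 40, no missing data.**
- Normal data, 6,000 runs per case. Equal correlations: 0.997. Correlation decaying over time with measurement noise: 1.046, 1.076 and 1.115. Decaying without noise: 1.146. Decaying without noise and SD falling to 0.7: 1.367.
- Tender-joint-like counts (baseline mean about 14, minimum 3), mean reductions of 20/35/50/60% on sonelokimab and 10/15/22/28% on placebo, four scenarios of 600 runs: 1.175, 1.146, 1.079 and 1.117.

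**Scale.** √1.05 = 1.025 and √1.18 = 1.086, so 5–18% in variance is about 2–9% in interval width. In participants: 40 − 40/1.05 = 1.9 and 40 − 40/1.18 = 6.1 per arm.

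**Protocol model.** With no baseline term and change as the outcome, b_c is replaced by 0. With correlation 0.5 and constant SD the ratio is 1 + 0.25/0.75 = 1.333. Across the assumed structures the Week 12 variance would be about 13% to 134% higher than with visit-specific slopes.

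**The case against.** The strongest reply is that a baseline main effect is a legitimate, parsimonious choice and these analyses lie outside the confirmatory hierarchy. Under randomization with complete data the treatment estimate is unbiased and its model-based SE reflects the extra variance, so neither validity nor type I error is at risk. Protocol 12.3 leaves technical detail to the SAP, and the SAP already supplies baseline. A large loss needs fading correlation with baseline. Shrinking SDs alone cost very little, and the documents supply nothing to choose between these cases. All of that stands. It makes this an efficiency point of uncertain size.

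Several stronger readings are tempting and do not hold:
- *Every continuous endpoint is affected.* mNAPSI has one post-baseline visit in Part A, so its gain is exactly zero, and no MMRM is named for LDI.
- *Early visits always set the slope, and every Week 12 interval is wider.* Both depend on the correlation structure. With a constant slope the loss is nil.
- *The protocol model has the same fault.* It contains no baseline, so it has no slope to share. Its gap is the missing main effect, which the SAP repairs without saying so.
- *Proportional improvement steepens the slope for hs-CRP too.* SAP 8.6.2.8 analyses hs-CRP on the log scale, where a proportional fall is a constant shift. Any loss there rests on fading correlation alone.
- *Week 12 is the designated time point for all continuous secondary endpoints.* Protocol 7.2.3 refers to specified time points, and effects are extracted at each visit.
- *The missing-at-random adjustment is damaged.* The simulations had no missing data, so this is untested.

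**Conclusion.** The omission is plain in the text: the operative SAP model has a treatment-by-visit term but no baseline-by-visit term, and the protocol model has no baseline term. The consequence is a possible loss of Week 12 precision for endpoints analysed by MMRM with two or more Part A post-baseline visits, chiefly TJC68, SJC66, PtAAP, PtGADA, PhGADA and HAQ-DI.

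The Week 12 variance is about 0–2% higher when the slope is constant or correlations are equal, and roughly 5–18% higher when correlation with baseline fades. Harsher assumptions go further, up to 1.37 in the most extreme case run. The range rests wholly on assumed SDs and correlations. No bias or type I error problem follows, and the ACR50, ACR20 and PASI90 tests, which use logistic regression, are untouched. The change is a free improvement, worth making because the model description needs reconciling anyway.

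**What to change.** In SAP 8.6.1.2, specify the fixed effects as treatment, visit, treatment-by-visit, baseline, baseline-by-visit, sex and prior biologic exposure. For log-transformed hs-CRP, use log baseline and log baseline-by-visit. In SAP Section 9, list the added baseline terms as a change from protocol 12.3.3.2, so that it is clear which model governs.

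The cost is at most three more parameters with four Part A visits (fewer for other schedules, none for mNAPSI) in about 200 participants, plus one line in Section 9. No new data are needed. If the slope is in fact constant, the penalty is negligible (simulated variance ratio 0.997).

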#### **12.3.3.3 Pharmacokinetic Analyses**

Serum concentration data for sonelokimab will be listed and summarized using descriptive statistics. Serum sonelokimab concentration results may be used for other analyses (e.g., population PK modeling), which will be reported separately.

#### **12.3.3.4 Immunogenicity Analyses**

ADA data for sonelokimab will be listed and summarized using descriptive statistics. Results may be used to support other analyses (e.g., population PK modeling), which will be reported separately.

#### **12.3.3.5 Part B Analysis**

For the Part B analysis, no confirmatory statistical testing will be performed. All efficacy endpoints will be seen as secondary, and descriptive statistics will be presented by visit from Week 0 to Week 24 and repeated by visit from Week 12 to Week 24.

For other secondary dichotomous endpoints, a non-responder imputation method, accounting for visits missed due to COVID-19, will be used. For continuous endpoints, no imputation is planned.

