## **8.8 Protocol Deviations**

All deviations from planned study procedures are to be recorded. Protocol deviations will be reviewed as part of the ongoing data cleaning process.

Prospective approval of protocol deviations, also known as protocol waivers or exemptions, are not permitted.

If there are restrictions to the clinical study as a result of the COVID-19 pandemic, it may be necessary to adjust the visit schedule, convert in-person visits to telephone contacts, and postpone study procedures until the next available study visit. All temporary mechanisms utilized, and deviations from planned study procedures in response to COVID-19 are to be documented as being related to COVID-19 and will remain in effect only for the duration of the public health emergency.

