## 7.2 Visit Windows

Visit windows will be used for all scheduled assessments. To allow for unscheduled and discontinuation assessments, the data will be summarized using the assessment (whether reported as a scheduled or unscheduled visit) closest to the nominal visit date, calculated from the first day of dosing. The visit result will be missing if no assessment was reported within the specified visit window around the scheduled date. If two assessments are equidistant from a scheduled visit, the earlier of the two will be used.

The visit windows will be calculated by bisecting the scheduled visit assessments. The upper limit of each window will be the mean of the two adjacent planned study days, rounded down to the nearest integer. The lower limit of each window will be the upper limit of the preceding window plus one, except for the first post-treatment visit which will start at 2.

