## Dichotomous Efficacy Endpoints

For all dichotomous endpoints, a non-responder imputation method will be used for the primary analysis. Participants will be considered non-responders if:

- They discontinue the study prior to the Week 12 visit for Part A or prior to the Week 24 visit for Part B and Part A+B (due to any reason). All future visits following the discontinuation will be imputed, or
- Have missing data for the endpoint of interest at baseline or at any intermediate time points. All visits with a missing assessment will be imputed, or
- Take prohibited protocol medication prior to the Week 12 visit for Part A or Week 24 visit for Part B and Part A+B. All future visits following the start date of the prohibited medication will be imputed.

In addition, two sensitivity approaches will be used for the dichotomous primary and key-secondary endpoints for analyses data:

1. The method for handling missing data will be dependent on the reason the data are missing. If a participant has discontinued due to lack of efficacy or an adverse event or starting prohibited medication the data will be imputed as a non-response. If the data are missing for any other reason the data will not be imputed. A multiple imputation for primary and key secondary analysis will be used including all available data up to Week 12 to enable the inclusion of participants with missing data at Week 12.
2. No data will be imputed and the data analysed by visit based on the observed data only.

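### SAP 7.3.1 omits the COVID-19 allowance that protocol 12.3.3.5 sets for Part B non-responder imputation, and SAP 9 does not declare the departure

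*Combined protocol and SAP*

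**What the plan says.** Protocol 12.3.3.5, on Part B, states: "For other secondary dichotomous endpoints, a non-responder imputation method, accounting for visits missed due to COVID-19, will be used". It does not say how the accounting is to be done. The imputation text for the primary endpoint (12.3.2.1), the key secondary endpoints (12.3.3.1) and the other secondary endpoints in general (12.3.3.2) has no such phrase, so the allowance is particular to Part B. Protocol 12.3.3.2 hands the mechanics to the SAP: "For dichotomous endpoints, a non-responder imputation method will be done and details will be defined in the SAP".

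SAP 7.3.1 sets the scope with "For all dichotomous endpoints, a non-responder imputation method will be used for the primary analysis" and names Part B and Part A+B in its rules for discontinuation and for prohibited medication. On missed assessments, participants are non-responders if they "Have missing data for the endpoint of interest at baseline or at any intermediate time points. All visits with a missing assessment will be imputed". No reason for absence is exempted.

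COVID-19 enters the SAP's handling of data in one place only: section 8.3 lists pandemic-related deviations separately. SAP 9, which lists changes from the protocol, includes items as small as the BASDAI derivation but not this one.

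**The concern.** The protocol foresees pandemic absences. Section 8.8 lets sites "convert in-person visits to telephone contacts, and postpone study procedures until the next available study visit", and Appendix 3 accepts that quarantine may cause a scheduled visit to be missed. Joint counts, PASI and hs-CRP cannot be obtained by telephone, so a converted visit can leave an ACR or PASI response, or minimal disease activity, without data.

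Protocol 8.9 says that Part B will evaluate whether Q4W dosing maintains response from Week 12. Under the SAP rule, an absence that has nothing to do with efficacy is tabulated as lost response. This happens in up to nine treatment sequences drawn from arms of about 40, and US participants do not enter Part B (SAP 3.1).

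**Working it through.** The documents give no figure for this point, so there is none to reproduce. The check has three steps.

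**1. Rules side by side**

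| Item | Protocol | SAP |
|---|---|---|
| Part B visit missed for COVID-19 | 12.3.3.5: to be accounted for, method open | 7.3.1: non-response, no exception |
| Who defines the method | 12.3.3.2: the SAP | not defined |
| COVID-19 provision | 8.8 and Appendix 3: absences expected and documented | 8.3: listing only |
| Change declared | - | 9: no |

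The NRI/LOCF analysis added in SAP 8.6.2.1 does not close the gap. It carries Week 12 forward for US completers and for participants who switched arm, and sets all other missing data to non-response.

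**2. When an absence becomes a failure**

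SAP 7.2 says: "The visit result will be missing if no assessment was reported within the specified visit window around the scheduled date". Protocol 8.6 allows rescheduling up to Day +7 with medical monitor approval. Against the SAP 7.2 windows for the ACR components:

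- Week 14: 99 + 7 = Day 106; window 93-106, inside.
- Week 16: 113 + 7 = Day 120; window 107-127, inside.
- Week 20: 141 + 7 = Day 148; window 128-155, inside.
- Week 24: 169 + 7 = Day 176; window 156 onward, inside.

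If procedures are instead postponed to the next visit:

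- Week 14 moves to Week 16 (Day 113), outside its window.
- Week 16 moves to Week 18 (Day 127) and Week 20 to Week 22 (Day 155). Each is the last day of the right window, so attendance one day late falls outside. The PASI windows end on the same days.
- Week 24 is open-ended.

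Many delayed visits therefore still supply data. The failure rule applies to absences that are not made up within the window.

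**3. Size**

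Let *p* be the response rate among those seen and *m* the share with no assessment in the window because of COVID-19, taken as unrelated to response.

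- Imputed rate = *p*(1 - *m*), so loss = *p* x *m*.
- *p*: 40% is the design assumption for Week 12 ACR50 on sonelokimab (protocol 12.1); its use for Part B, and the upper value of 70%, are assumptions.
- *m*: 2-5%, assumed.

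| | *m* = 2% | *m* = 5% |
|---|---|---|
| *p* = 40% | 0.40 x 0.02 = 0.8 points | 0.40 x 0.05 = 2.0 points |
| *p* = 70% | 0.70 x 0.02 = 1.4 points | 0.70 x 0.05 = 3.5 points |

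If *m* is read as scheduled visits missed, recovery through the windows makes these upper figures.

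To show the effect in one group: with an assumed 20 participants, 2 of them absent, and 9 responders among the 18 seen, the imputed rate is 9/20 = 45.0% against 9/18 = 50.0% among those seen.

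**The case against.** The strongest reply is that little depends on this. Part B is descriptive, with no confirmatory testing (protocol 12.3.3.5, SAP 8.1). For Part B ACR50, SAP 8.6.2.1 shows an as-observed summary beside the imputed one. SAP 8.6.3.1 analyses ACR20 by the same methods, and SAP 8.6.3.2 gives PASI90 the same descriptive displays. An as-observed table already drops an absent participant from that visit. The windows recover many delayed visits, and the deviation listing lets affected participants be traced. The protocol also never defines the allowance, so the SAP was free to shape it.

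Much of this stands, and it limits the point. It does not remove it. No as-observed Part B summary is specified for ACR70, PASI75/100, minimal disease activity or BASDAI50 (SAP 8.6.4.2, 8.6.4.3, 8.6.4.4, 8.6.4.7). Nor is an as-observed table what the protocol promised: it removes dropouts from the denominator too, whereas the protocol calls for non-responder imputation with one exception. Freedom to define the allowance is not freedom to omit it without saying so.

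Two stronger readings are tempting and not supported. A reader might infer that every COVID-19 absence becomes a failure; the windows and the Day +7 rule show otherwise. A reader might also infer that the protocol requires such visits to be excluded from the denominator. It does not, and doing so leaves fewer than all FAS-B participants in the table at that visit.

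**Conclusion.** The protocol and SAP disagree, and the disagreement is undeclared. Its effect is confined to Part B rates under non-responder imputation, and its direction is fixed: an absent responder with no assessment in the window lowers the rate, and an absent non-responder leaves it unchanged.

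A reader might infer that all reported Part B response rates are understated. They are not: the as-observed summaries for ACR50, ACR20 and PASI90 are unaffected. No primary or key secondary test, type I error or power figure is touched.

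The size cannot be known from the documents. The 0.8-3.5 points rest on an assumed 2-5% of visits missed, an assumed 40-70% response, absence unrelated to response, and no recovery through the windows. The effect in a single sequence depends on group sizes that the documents do not give. This is a minor correction, worth making because it is cheap and keeps a written commitment.

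**What to change.** Add to SAP 7.3.1 a rule to this effect:

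> For Part B dichotomous endpoints, an assessment missing within its analysis window, with COVID-19 documented as the reason, is not imputed as non-response, unless the participant has already discontinued the study or taken prohibited medication.

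Then name the method. Leaving the participant out of that visit's numerator and denominator is one acceptable choice; multiple imputation is another. Keep the table with all missing assessments as failures as a sensitivity display. If the sponsor prefers the current rule, declare the departure in SAP 9 with a reason.

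The cost is small. Protocol 8.8 already requires pandemic-related deviations to be documented as such, and SAP 8.3 already lists them. The downside is that denominators differ slightly by visit or, with multiple imputation, a little more analysis work.
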